### Safety assessments

2.10

To ensure the safety of the participants, all data collection was conducted under the supervision of the program director. During each follow-up visit, the patients’ adverse reactions during the drug administration were recorded, especially subjective discomfort reactions such as gastrointestinal, cardiovascular and cerebrovascular reactions, in order to understand whether the drugs existed toxic side effects. In addition, the biochemical indexes of patients, particularly liver function and kidney function indicators, are examined at each follow-up visit to determine whether there is any damage to internal organs from the objective test results.

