Meanwhile, traditional Chinese medicine (TCM) is widely used in the treatment of anemia for activating blood circulation and removing blood stasis. It functions in many ways, such as engaging in multi-linked and multi-targeted regulation, improving the bone marrow hematopoietic microenvironment, restoring bone marrow hematopoietic function, and improving the quality of life of patients. Therefore, this study followed the principles of prospective, randomized, and controlled, aiming to explore the clinical efficacy of TCM methods on postoperative anemia in ITF patients who underwent PFNA, for the purpose of obtaining more completed information on safety and efficacy, and providing research methods and ideas for the treatment of postoperative anemia in ITF.

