### Study design

2.2

This study is a prospective, outcome assessor-, and data analyst-blinded randomized controlled clinical trial. The objective of this proposed study was to investigate whether Shengyu Decoction could improve the symptoms of anemia after PFNA in elderly ITF patients. Elderly patients with an emergency diagnosis of ITF at our institution from January 2022 to December 2023 were enrolled. All patients were treated with PFNA intramedullary fixation at our hospital.

The principal investigator (PI) is responsible for the overall project and organizing Steering Committee meetings. PIs of sub-center departments are responsible for gathering experts to carry out the project. An independent Steering Committee will be responsible for affairs such as participants’ safety, meetings, recruitment and follow-up of participants, and quality control. The coordinating center is responsible for communicating protocol modifications and providing materials. It consists of a 2-week treatment period and a 6-month follow-up period. Outcome assessment at baseline, post-operative days 1, 3, 7, 14 days, 1 month, 3 months, and 6 months postoperatively. (Fig. 1)

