### Intervention

2.4

Basic treatments: All patients in both groups were treated with preoperative rehydration, analgesia and anticoagulation, and the relevant departments were consulted to exclude preoperative contraindications; all patients were treated with PFNA intramedullary fixation; postoperative treatments such as rehydration, anticoagulation, analgesia, infection prevention and regular drug changes were given accordingly.

Treatment group: Patients in the trial group were treated with Shengyu decoction granules under basic treatment with 1 dose daily in 2 times for 14 days.

Control group: The control group was treated with placebo on the base treatment, and the placebo was simulated by Shengyu decoction granules, which were required to be free of the active ingredients of the test drug, and their color, taste and odor were similar to those of Shengyu decoction, and 1 dose was given daily in 2 doses for 14 days.

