### Blinding

2.8

All investigators, physicians, nurses, patients, assessors, statisticians, and participants remained blinded to group assignment until the trial ended, when all statistical analyses were finished. If any clinically significant adverse events occur after the first dose that are potentially treatment-related, the study physician will re-evaluate the participant and the PI will determine whether unblinded treatment is necessary. If non-blinding is required, the allocation information will be provided.

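### Section 2.10 words clinical harm recording as drug reactions during dosing; followed literally, it misses other clinical events and any that start after day 14

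*Protocol article*

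**What the plan says.** Section 2.10 (Safety assessments) has two parts. For clinical events, it says that at each follow-up visit patients' "adverse reactions during the drug administration were recorded, especially subjective discomfort reactions such as gastrointestinal, cardiovascular and cerebrovascular reactions"; the stated purpose is to learn whether the drug has toxic side effects. For the laboratory, it says that biochemical indexes, "particularly liver function and kidney function indicators, are examined at each follow-up visit", to detect organ damage.

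The time frame comes from two other sections. Section 2.2 says of the trial: "It consists of a 2-week treatment period and a 6-month follow-up period". Its assessments fall at baseline, on postoperative days 1, 3, 7 and 14, and at 1, 3 and 6 months. Section 2.4 says that the active arm is "treated with Shengyu decoction granules under basic treatment with 1 dose daily in 2 times for 14 days", and placebo runs for the same period.

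Two other features bear on the point. Both arms are anticoagulated before surgery, and afterwards "postoperative treatments such as rehydration, anticoagulation, analgesia, infection prevention and regular drug changes were given accordingly". Section 2.3 admits only patients whose hemoglobin on the first postoperative day is below 8 g/dL.

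Section 2.9 makes hemoglobin the primary outcome. It lists hidden blood loss as a secondary outcome, and 30-day readmission and mortality among the other outcomes.

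**The concern.** The sentence in section 2.10 carries two limits. The first is cause: it speaks of reactions, collected to judge the drug's toxicity. The second is time: it ties them to drug administration. A site that follows the sentence as written would not record a clinical event seen as a consequence of the fracture, the operation or the anticoagulant. Nor would it record any event that starts after dosing ends.

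In a randomised, placebo-controlled trial, the arms themselves answer whether the product causes harm: count every event and compare. Requiring a causal judgement on each event before it is recorded replaces that comparison with opinion. The risk is concrete here, because the Discussion itself notes that trauma and surgery can bring on cardiovascular complications, so an alternative explanation is always at hand.

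Bleeding matters twice over. It is a harm in anticoagulated, severely anemic patients, and it lowers hemoglobin. If bleeds are not recorded as events, a low hemoglobin value cannot be traced to its cause. Events that are never collected cannot be recovered by a later analysis plan.

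**Working it through.** The plan states no figure on this point, so there is nothing to reproduce. The check is a count of visits and a comparison of what each source of data can capture.

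**Time window**
- Length of dosing: 14 days (sections 2.2 and 2.4).
- Earliest start: postoperative day 1, because eligibility depends on that day's hemoglobin result (section 2.3). Dosing that starts then ends on about postoperative day 14.
- Postoperative visits: days 1, 3, 7 and 14, then 1, 3 and 6 months, which makes 4 + 3 = 7 (section 2.2).
- Visits after dosing: 1, 3 and 6 months, so 3 of 7.
- Time after dosing, taking 6 months as 182.5 days: 182.5 − 14 = 168.5 days. The dosing window is 14/182.5 = 7.7% of the period. This share describes only the literal window for clinical reactions, not safety recording as a whole.

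**What each source captures**

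| Source | Period | What it leaves out |
|---|---|---|
| Clinical reactions (2.10) | Dosing, read literally | Events not seen as drug reactions; any event starting after dosing |
| Biochemistry (2.10) | Each follow-up visit | Clinical events that leave no mark on these tests |
| Mortality (2.9.2) | No end date given | All non-fatal events |
| 30-day readmission (2.9.2) | 30 days | Events in the index stay, events not leading to readmission, and events after day 30 |
| Hemoglobin and hidden blood loss (2.9) | Outcome visits | The cause of a fall; both are efficacy outcomes |

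Set side by side, two gaps remain. One is a non-fatal clinical event during the index stay that is put down to surgery or anticoagulation. The other is a non-fatal clinical event after day 30. Within section 2.10 itself, the laboratory part looks for late harm while the clinical part, read literally, does not.

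**Effect of filtering by cause**

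Suppose *a* events of one kind occur in the active arm and *b* in the control arm, and each is attributed to the operation or the anticoagulant. The recorded counts are then 0 and 0, whatever *a* and *b* are. A true excess *a* − *b* disappears. Blinding, if it holds, makes the filter act alike in both arms, but it does not bring back the filtered events.

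**Scale**

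The article gives no rate for any adverse event, so the number lost cannot be derived. For context, with 36 patients per arm (section 2.11), even complete recording with no event in an arm leaves a one-sided 95% upper limit of 1 − 0.05^(1/36) = 8.0%. Safety information in a trial of this size is thin to begin with.

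**The case against.** The strongest reply is that the sentence is loose English in a condensed article. It places the recording at each follow-up visit, so some recording continues to 6 months, and the reference to drug administration may describe exposure rather than onset. The word reactions may simply mean events. Nothing says that an investigator must attribute an event to the drug before writing it down. Section 2.6 mentions a data collection form that covers all potential risks, and section 2.2 makes a steering committee responsible for participants' safety. All this is fair, and it is why the point rests on a literal reading. It does not remove the point: the sentence is the only stated rule for clinical events, and its plain wording sets both limits.

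Four stronger readings are tempting, and the article does not support them.
- *Safety recording as a whole stops at day 14.* It does not: biochemistry, mortality and 30-day readmission are also collected.
- *Bleeding and thrombosis are excluded because they are not named.* The named categories are examples in an open list, and cardiovascular and cerebrovascular reactions could include some thrombotic events. A full list of events is something an article commonly leaves to the full protocol.
- *The product itself promotes bleeding.* The phrase "widely used in the treatment of anemia for activating blood circulation and removing blood stasis" describes traditional Chinese medicine in general, not Shengyu Decoction.
- *Section 2.8 contradicts section 2.10.* Section 2.8 applies if "any clinically significant adverse events occur after the first dose that are potentially treatment-related", and it governs re-evaluation and unblinding. It is not a recording rule, so it neither conflicts with section 2.10 nor fills the gap.

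**Conclusion.** The point holds as a defect in the stated recording rule, and it is cheap to mend. Taken literally, section 2.10 confines clinical event capture to suspected drug reactions in the 14-day dosing period. Three of the seven postoperative visits then have no rule for new clinical events. The other sources do not close the gap for non-fatal events in the index stay or after day 30.

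The conclusion assumes that sites would apply the sentence as written and that no fuller document overrides it. It does not depend on any event rate or on any property of the product. That both arms are anticoagulated, and that all patients enter with hemoglobin below 8 g/dL, is enough to make bleeding relevant both as a harm and to the primary outcome. The point does not call the hemoglobin comparison itself into question.

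**What to change.** Reword section 2.10 so that all adverse events are recorded regardless of judged cause, from first dose through the scheduled 6-month visit, and are tabulated by arm. The investigator's view on causality can still be noted for each event, but as a descriptor and not as a condition for recording it.

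As a secondary addition, give bleeding and thromboembolic events their own categories on the case report form. Bleeds can then be counted as harms and set beside the hemoglobin results.

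The cost is protocol wording, a few form fields and slightly more recording work at visits that already take place. The change affects data collection only; treatment and visit schedule stay as they are. It has to be made before events are missed.

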### Sample size calculation

2.11

The sample size estimation was based on the mean and standard deviation of the primary efficacy parameters with reference to the pretest. α= 0.025, 1 sided test, and β = 0.10 were established. According to the results calculated by PASS 15.0 software (NCSS, LLC. Kaysville, UT, USA), 30 patients per group were required. Due to an estimated dropout rate of 20%, 36 patients were eventually included in each group.

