### Randomization and allocation

2.5

After qualifying for screening, patients will be randomized into 2 groups with an allocation ratio of 1:1. The randomization will be created via SAS PROC PLAN software (SAS Inc., Cary, NC) by an independent third-party clinical research organization (Institute of Basic Research in Clinical Medicine, China Academy of Chinese Medical Science) and hid from the researchers by a senior data manager who is not involved in the study. The group assignment list will be sealed in light-blocking envelopes and be opened by the researchers following informed consent procedures and baseline testing.

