### Statistical analyses

2.12

A detailed statistical analysis protocol will be formulated prior to all analyses. All data will be analyzed in the clinical research center of Longhua Hospital affiliated to Shanghai University of TCM by statisticians blinded to allocation using the SPSS 20.0 statistical software (SPSS Inc., Chicago, IL). After evaluating the data distribution, 2-sample t-test (or Wilcoxon rank-sum test) will be used for the analysis of continuous variables. For categorical data, the Chi-Squared test (or Fisher exact test) will be used. Outcome variables including hemoglobin concentration, hidden blood loss, HHS scores for hip joint-specific function will be summarized with means and SDs. For statistical analysis of continuous outcomes, changes in the scores before and after treatments will be regarded as dependent variables, with the baseline scores and research institutions as covariates and the groups as fixed factors, to perform the analysis of covariance. To verify the trends for each visit in the 2 groups, repeated measures analysis of variance will be performed. For categorical outcome data, the Chi-Squared test (or Fisher exact test) will be used.^[16,17]^

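### Minor arithmetic error: at the expected 20% dropout, 36 patients per group leave 28.8 evaluable, below the 30 that section 2.11 requires; 38 per group would be needed

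*Protocol article*

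**What the plan says.** All the relevant figures are in the protocol article, section 2.11 (Sample size calculation).

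- Source of the effect and spread: "The sample size estimation was based on the mean and standard deviation of the primary efficacy parameters with reference to the pretest". The article prints neither value.
- Error rates: "α= 0.025, 1 sided test, and β = 0.10 were established", so the target power is 90%.
- Result before any allowance for dropout: "30 patients per group were required".
- Result after the allowance: "Due to an estimated dropout rate of 20%, 36 patients were eventually included in each group".

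Two other places bear on the check. Section 2.5 (Randomization and allocation) fixes equal allocation: "patients will be randomized into 2 groups with an allocation ratio of 1:1". Section 2.12 (Statistical analyses) names the basic test: "2-sample t-test (or Wilcoxon rank-sum test) will be used for the analysis of continuous variables". It also plans an analysis of covariance on change, with the baseline value among the covariates. No other section gives a different sample size, dropout rate or definition of dropout.

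**The concern.** A dropout rate applies to the patients enrolled, not to the patients who remain. To end with a required number after a proportion is lost, one divides the required number by the proportion kept. Adding 20% to the evaluable number is a common slip and always gives too small a figure. Here the enrolled number matches that slip exactly.

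Section 2.11 holds the article's only statement of sample size and power. As printed, the requirement, the dropout estimate and the planned number cannot all be true together. If the three figures are carried into the trial report, the report will claim that the sample size allows for 20% dropout at 90% power when the arithmetic does not support this.

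**Working it through.** **Inputs** (section 2.11 unless noted): 30 required per group; dropout 20%; 36 planned per group; alpha 0.025 one-sided; power 90%; 1:1 allocation (section 2.5); two-sample t-test (section 2.12). The mean difference and standard deviation are not given, so the base figure of 30 cannot be rebuilt and is taken as stated.

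**1. Reproduce the planned figure.** 30 × (1 + 0.20) = 36. The match is exact, but the formula is inferred.

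**2. Apply the stated dropout to it.** 36 × (1 − 0.20) = 28.8 evaluable per group, 1.2 short of 30.

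**3. Dropout that 36 per group can absorb.** 1 − 30/36 = 16.7%.

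**4. Number that satisfies both stated figures.** 30 / (1 − 0.20) = 37.5, rounded up to 38 per group. The total is 2 × 38 = 76 against 2 × 36 = 72, a gap of 2 per group and 4 overall. With 38 enrolled, 38 × 0.80 = 30.4 remain.

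**5. Effect on power.** Because the effect size is not published, it is solved backwards from the assumption that 30 per group gives exactly 90% power with an unadjusted test.

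- Normal approximation: d = (1.960 + 1.282) × √(2/30) = 0.837. At 28.8 per group, d × √(28.8/2) − 1.960 = 1.216, which gives power of 88.8%.
- Noncentral t: d = 0.851.

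| Evaluable per group | Power, noncentral t, d = 0.851 |
|---|---|
| 30.4 | 90.4% |
| 30 | 90.0% |
| 28.8 | 88.8% |
| 28 | 87.9% |

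**6. Allow for rounding in the 30.** If the unrounded requirement was just above 29, then d is close to 0.866 (the value at which 29 per group gives 90%). Power at 28.8 is then 89.8%. So at the expected evaluable number, power lies between about 88.8% and 89.8%, which is 0.2 to 1.2 points below 90%.

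**7. Allow for chance in the number lost.** With binomial dropout of 20% in each arm and d = 0.851, average power is 88.5% with 36 enrolled per group and 90.2% with 38.

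**The case against.** The strongest reply is that the power loss is small and rests on assumptions. The pretest mean and standard deviation are not printed, so every power figure above comes from a back-solved effect and an unadjusted t-test. Section 2.12 also plans covariance adjustment for baseline, which could recover the lost information. The evaluable fraction of the requirement is 28.8/30 = 0.96. If the pretest standard deviation was that of the post-treatment value, adjustment multiplies the variance by about 1 − r², and a baseline correlation of 0.20 or more would be enough. If it was the standard deviation of change, the factor is (1 + r)/2, and any correlation up to 0.92 would be enough. Which standard deviation was used is unknown, and the entry criterion of hemoglobin below 8 g/dL in section 2.3 may weaken the correlation.

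This part stands: a reader might infer from the arithmetic that the trial is underpowered, or that 90% power is certainly not delivered, and the document does not support either. What it does not remove is the contradiction among the printed figures. Section 2.11 claims no gain from adjustment, and it enlarges the sample because of dropout, so it treats those patients as lost to the analysis. Rounding of less than one patient in the 30 does not close a gap of 1.2.

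Nor is this a detail that an article may leave to a fuller document: the figures are all printed, and they disagree.

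**Conclusion.** The point holds as a minor arithmetic error. On the protocol's own figures, 36 per group does not preserve 30 evaluable patients at 20% dropout; 38 per group would. That conclusion needs no assumption beyond applying the dropout rate to the patients enrolled.

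The shortfall of 0.2 to 1.2 points is conditional. It assumes that 30 per group gives 90% power (exactly, or after rounding up), that dropouts are not analysed, and that the test is unadjusted. A loss of that size changes no design decision or analysis, so the error should not be presented as a threat to the trial. That the figure came from multiplying by 1.2 is an inference from the exact match.

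**What to change.** Correct one sentence in section 2.11. Keep 36 per group (72 in total) and the 20% dropout estimate, and state that about 28.8 patients per group are then expected to be evaluable, with power slightly below 90%. The figure is about 89% on the assumptions above; the sponsor should recompute it from the pretest mean and standard deviation before printing it.

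It is fair to add that 36 per group would hold 30 evaluable at 16.7% dropout, but that figure should not replace the 20% estimate, because this would fit the assumption to the number.

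If the sponsor wants 90% power after 20% dropout to stand, state 38 per group (76 in total) instead.

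The first option costs a reworded sentence and a slightly less favourable power figure. The second costs 4 more patients.

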### Statistical analyses

2.12

A detailed statistical analysis protocol will be formulated prior to all analyses. All data will be analyzed in the clinical research center of Longhua Hospital affiliated to Shanghai University of TCM by statisticians blinded to allocation using the SPSS 20.0 statistical software (SPSS Inc., Chicago, IL). After evaluating the data distribution, 2-sample t-test (or Wilcoxon rank-sum test) will be used for the analysis of continuous variables. For categorical data, the Chi-Squared test (or Fisher exact test) will be used. Outcome variables including hemoglobin concentration, hidden blood loss, HHS scores for hip joint-specific function will be summarized with means and SDs. For statistical analysis of continuous outcomes, changes in the scores before and after treatments will be regarded as dependent variables, with the baseline scores and research institutions as covariates and the groups as fixed factors, to perform the analysis of covariance. To verify the trends for each visit in the 2 groups, repeated measures analysis of variance will be performed. For categorical outcome data, the Chi-Squared test (or Fisher exact test) will be used.^[16,17]^

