### Patient population and recruitment procedure

2.6

Participants will be recruited from Longhua Hospital affiliated to Shanghai University of Traditional Chinese Medicine. Those patients eligible for enrollment and willing to participate in the study were initially evaluated at baseline and then finally identified through a combination of clinical presentation, physical examination, imaging and laboratory tests. Considering the age of the patients enrolled in this study, the investigator must obtain the consent of the patient's immediate family besides the patient's own informed consent to start the trial. Participants will be informed about the required cooperation in the study, the potential benefits of participating in the study, the possible adverse effects, risks and discomforts of participating in the study, and the associated reimbursement costs and confidentiality of personal information. Participants will also be informed of withdrawal from this study at any time during the study and that the investigator may discontinue your participation in this study at any time out of concern for your best interests. A data collection form including all variables of interest and all potential risks will be completed by the corresponding research center. All information obtained will be kept in an e-database for future statistical analysis. Recruitment will start in January 2022 and is expected to end in December 2023. Final follow-up of all participants will be completed on December 31, 2024.

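### The repeated-measures ANOVA named for visit trends would, in its standard SPSS form, drop every patient with one missing visit; a mixed model would keep the data already collected

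*Protocol article*

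**What the plan says.** Section 2.12 of the protocol article names the analysis that uses all visits together: "To verify the trends for each visit in the 2 groups, repeated measures analysis of variance will be performed". The work is to be done "using the SPSS 20.0 statistical software"; the SPSS procedure is not named. The same section also plans two-sample tests and an ANCOVA of the change from before to after treatment, adjusted for baseline and centre. None of these is labelled primary. The section promises a detailed analysis protocol before any analysis.

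Section 2.2 gives the schedule: "Outcome assessment at baseline, post-operative days 1, 3, 7, 14 days, 1 month, 3 months, and 6 months postoperatively". On duration it says: "It consists of a 2-week treatment period and a 6-month follow-up period".

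Section 2.11 states that "30 patients per group were required", and then: "Due to an estimated dropout rate of 20%, 36 patients were eventually included in each group".

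Two other places bear on who might have missing visits. Section 2.9.2 lists mortality among the other outcomes. Section 2.6 tells participants that "the investigator may discontinue your participation in this study at any time out of concern for your best interests".

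**The concern.** Classical repeated-measures ANOVA works on a rectangular data set with one value per patient per visit. The standard SPSS repeated-measures procedure therefore deletes listwise: a patient with any visit missing leaves the analysis altogether, including the visits that were attended.

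That fits this trial poorly. The patients are aged 60 to 85, have had a hip fracture and are followed for six months. A patient who dies or is lost after day 14 may have complete haemoglobin data for the whole 14-day treatment period, and all of it would be thrown away because a month-3 or month-6 value is absent. The trend analysis would then describe only patients who survived and attended every visit.

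Two things are at stake. One is precision. The other, more important here, is selection: if leaving the study depends on the patient's condition, and does so differently in the two arms, the arms compared are no longer the arms randomised.

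**Working it through.** **Inputs from the protocol article.** Required 30 per group; 36 per group enrolled; dropout 20%; one-sided α = 0.025; β = 0.10, so power 90% (all section 2.11). Eight assessments (section 2.2). Entry depends on the day-1 haemoglobin (section 2.3), so six assessments follow it (days 3, 7, 14; months 1, 3, 6), or seven if day 1 is counted as post-baseline.

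**Inputs not in the article.** No mean, SD, missed-visit rate or death rate is given. The article does not say which outcome is measured at which visit; below, the outcome is assumed to be measured at all of them.

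**Step 1, the plan's own figure.** 30 × (1 + 0.20) = 36, which matches. (Dividing, 30 / (1 − 0.20) = 37.5, rounds up to 38; that is a separate point.)

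**Step 2, complete cases from dropout alone.** 36 × 0.80 = 28.8 per arm, or 57.6 of 72 in total. This is a ceiling, because it supposes that every patient who does not drop out attends every visit.

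**Step 3, the effect size implied by 30 per group.** Normal approximation: d = (1.960 + 1.282) × √(2/30) = 0.837. With the noncentral t distribution (df = 2n − 2, noncentrality d√(n/2)), the d that gives 90% power at n = 30 is 0.851.

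**Step 4, cost of the lost patients for a simple two-group comparison.** At that d, power is 90.0% with n = 30 and 88.8% with n = 28.8, by either method.

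**Step 5, sensitivity to missed single visits.** Complete cases per arm = 36 × 0.80 × (1 − m)^k, where m is an assumed, independent missed-visit rate among patients who do not drop out, and k = 6 or 7.

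| Assumed m | Complete cases per arm (k = 6; k = 7) | Two-group power at implied d |
|---|---|---|
| 0% | 28.8; 28.8 | 89% |
| 1% | 27.1; 26.8 | 86–87% |
| 2% | 25.5; 25.0 | 84–85% |
| 3% | 24.0; 23.3 | 81–83% |
| 5% | 21.2; 20.1 | 75–78% |
| 10% | 15.3; 13.8 | 58–64% |

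Only the first row rests on the article's dropout figure alone. The powers show what losing n costs a two-sample comparison. They are not the power of the repeated-measures test, which depends also on the within-patient correlation and the number of visits.

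**Step 6, comparison.** A likelihood-based mixed model keeps every patient with at least one post-baseline value, so up to 36 per arm contribute.

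**The case against.** The strongest reply is that this is a supporting analysis. Section 2.12 gives it the task of checking trends, while the comparison of continuous outcomes is assigned to the ANCOVA of change. That ANCOVA needs only the before and after values, so it does not lose a patient for missing some other visit. This stands. It limits the point to the trend analysis, although the article does not say which analysis is primary.

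Three stronger readings are tempting and are not supported:

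- *The trial's power falls to roughly 77–82%.* Figures of that order need an assumed missed-visit rate of about 3–5% stacked on the full 20% dropout, and section 2.11 does not define whether dropout already includes patients with incomplete visits. They are also two-sample powers, and nothing says the trial was sized on the repeated-measures test.
- *The deleted patients are the sickest.* Mortality as an outcome and the investigator's freedom to end participation make this plausible. But the article gives no reasons for dropout, no death rate and no missingness mechanism, so it is not shown.
- *Visits spaced from 2 days to 3 months apart invalidate the test through sphericity.* A Greenhouse-Geisser correction or the multivariate test handles that within ANOVA, and the choice can be left to the analysis plan. Neither brings back deleted patients.

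It can also be said that detail is deferred to a later analysis protocol, which might add imputation or a long-format model. That is possible, and it is why deletion is described here as what the standard form does. It does not undo the choice: the article names a method, and in its usual form that method needs complete data.

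**Conclusion.** The point holds as a recommendation on the trend analysis. The named method, in its standard SPSS form, would use at most about 28.8 of 36 patients per arm under the planned dropout, and fewer if single visits are missed. It would discard observed early haemoglobin from patients who leave later, and it would be open to selection if missingness relates to the patient's condition.

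The size and direction of any bias cannot be computed from the article. The loss of numbers from dropout alone is minor (about 89% against 90% for a simple two-group comparison, at a back-calculated d of about 0.85), so the case for change rests mainly on discarded data and possible selection. The ANCOVA of change is not subject to this deletion.

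The conclusion assumes that the usual procedure is used without imputation and that the outcome is analysed over the full schedule. If haemoglobin were modelled only to day 14, losses after day 14 would not remove patients.

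**What to change.** In section 2.12, replace the repeated-measures ANOVA with a linear mixed model for repeated measures:

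- Fixed effects: group, visit, group-by-visit, baseline value and baseline-by-visit.
- Covariance: unstructured, with a simpler structure chosen by a prespecified rule if the model does not converge.
- Data: all randomised patients' available post-baseline visits.
- Software and output: the MIXED procedure in SPSS, reporting the group difference at each visit.

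State with it that the model assumes data missing at random, say how visits after death are treated, and add one sensitivity analysis for missing data. The mixed model does not by itself resolve dropout that depends on unobserved values, which is why the sensitivity analysis is needed.

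The cost is revised wording, different syntax in the same software and slightly more modelling work. The downside is reliance on the missing-at-random assumption. No additional patients or visits are required.
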